**Discussion:**

The BAPS will provide data on the 5-year incidence of PACS progressing to PAC or PACG and determine the risk factors for disease progression. This study will also help redefine high-risk patients with PACS.

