### Sample size estimation

Currently, many studies have reported the prevalence of PACS in the population, with rates ranging from 4.68% (95% Confidence Interval [CI]: 4.541–4.819%) to 10.4% (95% CI: 9.6–11.2%) (7–9, 18–21). However, few studies have investigated the incidence of PACS progressing to PAC or PACG (11, 12, 15, 22, 23). In a population-based prospective study conducted in India, 11 out of 50 PACS eyes (22%; 95% CI: 9.8–34.2%) developed PAC over 5 years (23). Another follow-up study in Denmark involving 75 PACS eyes reported a progression incidence of 16% (15). Given the similarity between our sample characteristics and those in the Indian study, we conservatively estimated the incidence of PACS progressing to PAC or PACG at 20%. To analyze the risk factors, we plan to collect a larger sample size than previous studies. Considering the number of candidate risk factors and the prevalence of PACS, we will use standard sample size calculation formulas for proportions, aiming for a desired level of statistical power of 80% and a significance level of 0.05. Based on these calculations, we estimate that 700 subjects are needed to achieve reliable results. Accounting for an anticipated attrition rate of up to 15%, we set the final sample size at 825 individuals, expecting to have complete follow-up data for 700 individuals at the end of the study.

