### Statistical analysis plan

All parameters measured in UBM will be calculated by averaging the corresponding measurements from both horizontal and vertical images. The normality of the data will be evaluated by using the Shapiro–Wilk test. Means and standard deviations will be calculated for all continuous variables. Baseline characteristics will be compared between progression group and non-progression group using the independent *t*-test or Mann–Whitney U test for continuous variables and the Pearson chi-square test for categorical variables.

The primary outcome is the progression rate, in other words, the rate of acute PAC (IOP > 21 mmHg) and the proportion of eyes developing PAS. We will evaluate the risk factors for PACS progression to PAC or PACG using univariable and multivariable logistic regression analysis, as well as Cox regression analysis. All statistical analyses will be performed using the software SPSS 22.0 (SPSS, Inc., Chicago, IL) with a significance level set at 0.05.

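### The sample-size section says 700 subjects allow for the number of candidate risk factors, but gives no such number, while about 40 to 48 listed variables face one uniform 0.05 threshold on roughly 140 expected events

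*Protocol article*

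**What the plan says.** Finding risk factors is half of the principal aim (Study design and principal aims). The abstract gives the intended use: "This study will also help redefine high-risk patients with PACS".

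The Statistical analysis plan section compares baseline characteristics between progressors and non-progressors one variable at a time. It then evaluates risk factors "using univariable and multivariable logistic regression analysis, as well as Cox regression analysis". All of this is done "with a significance level set at 0.05", and Table 1 repeats that level. The section states no rule for moving variables from the univariable to the multivariable models.

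The Sample size estimation section assumes 20% progression and describes a calculation made "Considering the number of candidate risk factors and the prevalence of PACS", "aiming for a desired level of statistical power of 80% and a significance level of 0.05". It concludes that "we estimate that 700 subjects are needed to achieve reliable results". It names formulas for proportions as the method. It does not say how many candidate factors were considered, what effect was to be detected, or what precision was wanted.

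**The concern.** The sample-size sentence tells the reader that 700 was matched to the number of risk factors under study. A formula for one or two proportions takes a rate, a difference or precision, alpha and power; the number of candidate predictors is not among its inputs. The claim is therefore unsupported as published.

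This matters because the list of measurements is long. The Questionnaire and Ophthalmologic examinations sections describe about 40 to 48 baseline variables, many measuring nearly the same thing. Anterior chamber depth comes from the IOLMaster, AS-OCT and UBM. Angle opening distance and trabecular-iris space area are each taken at two distances. If this list goes through tests at 0.05 with about three events per variable, some reported risk factors are likely to be chance findings, and the real ones are likely to look stronger than they are. Those results are intended to identify which patients count as high-risk.

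**Working it through.** **1. The plan's own figures.** Enrolment: 700/(1 − 0.15) = 823.5, so 824 against the stated 825; conversely 825 × 0.85 = 701. The step from 700 to 825 reproduces.

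The 700 itself does not follow from the stated inputs. Three guesses come close:
- a one-sample test of 20% against 16% (two-sided 0.05, 80% power): 696;
- a 95% confidence interval of ±3 points around 20%: 1.96² × 0.2 × 0.8/0.03² = 683;
- ten events per variable with 14 variables: 14 × 10/0.20 = 700.

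The article names none of them.

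**2. Number of listed variables.** Personal history 9, medical history 3, clinical examination 6 (presenting and corrected acuity, IOP, lens grade, limbal chamber depth, gonioscopy), IOLMaster 7, AS-OCT 4, nerve fibre layer 1, UBM 14: total 44. Depending on how duplicates, ocular history and age are counted, 40 to 48 is a fair range. This is a count of what is collected, not a candidate list given by the article.

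**3. Events.**

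| Basis | Events | Per variable (44) |
|---|---|---|
| 20% of 700 | 140 | 3.2 |
| 20% of all 825 (upper bound if Cox uses partial follow-up) | 165 | 3.75 |
| 5.3% of 700 | 37 | 0.8 |
| 25.5% of 700 | 179 | 4.1 |

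The 5.3% and 25.5% are the ends of the Asian range in the Introduction. That sentence gives no follow-up period, so reading them as 5-year rates is an assumption. At 140 events, 40 to 48 variables give 3.5 to 2.9 events each.

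**4. Univariable false positives if all are null.** Expected number = 0.05 × k: 2.0, 2.2 and 2.4 for k = 40, 44 and 48. Correlation does not change this expectation. The chance of at least one does depend on it: 1 − 0.95^44 = 0.895 holds only under independence.

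**5. Survival through a multivariable step.** The article states no selection rule, so one was assumed: univariable p < 0.05, then multivariable p < 0.05. Simulation used 700 subjects, about 20% events, 44 candidates in four blocks and 150 runs per scenario.
- All null: at least one false factor survives in about 0.91 of runs if independent, 0.46 with within-block correlation 0.6, and 0.21 with 0.8.
- Three true factors, correlation 0.6: at least one false factor survives in about 0.4 of runs. Retained true log-odds ratios are inflated about 1.4-fold (true OR 1.2 per SD) or 1.3-fold (true OR 1.3).

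**6. Parameters that 700 supports.** Criterion for expected shrinkage S = 0.9: n = p/[(S − 1) ln(1 − R²cs/S)]. At 20% incidence the maximum Cox-Snell R² is 1 − exp[2(0.2 ln 0.2 + 0.8 ln 0.8)] = 0.632.
- Nagelkerke 0.10: R²cs = 0.063, 137 subjects per parameter, so 700/137 = 5.1 parameters.
- Nagelkerke 0.15: R²cs = 0.095, 90 per parameter, so 7.8.
- Nagelkerke 0.25: R²cs = 0.158, 52 per parameter, so 13.5.

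The R² values are assumptions. The formula is for a binary outcome and serves here as a guide for the Cox model.

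**The case against.** The strongest reply is that candidate lists, selection rules, multiplicity control and validation usually sit in a full analysis plan, which is not shown. Their absence from an article is not itself an error. That stands, and the point does not rest on it. It rests on two things the article does state: that 700 allows for the number of candidates, and that 0.05 applies to every analysis.

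Several stronger readings are tempting and should be resisted.
- A reader might infer that every measured variable will be tested. No section says so, and eligibility already restricts some of them (IOP, prior surgery or laser). A short list of 14 would fit 700 as well, though the article does not give one.
- A reader might infer that univariable p-values will decide entry to the multivariable model. The text lists both kinds of model without linking them. Dropping that inference does not remove the problem: with all 44 variables entered, four of them true, the other 40 would still give about 0.05 × 40 = 2 nominal false positives.
- A reader might treat 140 events as a ceiling. It is an expectation in completers; the article's own figures allow more as well as fewer.
- A reader might quote the 90% chance of a false finding. That needs independence, which near-duplicate measurements contradict.

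It can also be said that shrinkage and calibration are prediction-model standards and that no risk score is planned. That is fair for a purely exploratory report. It is less persuasive if the results are used to define a high-risk group.

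**Conclusion.** The concern holds in limited form. The statement that 700 accounts for the number of candidate risk factors is unsupported: no number is given, and the cited type of formula does not use one. Against the roughly 40 to 48 listed variables, the assumed 20% yields about 3 events per variable. The quoted Asian range moves this only between 0.8 and 4.1.

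If the uniform 0.05 rule were applied to all of them and all were null, about 2 univariable false positives would be expected. Effects kept on significance would probably be overstated, by about 1.3- to 1.4-fold in the simulated settings. How often a false factor survives a multivariable model cannot be fixed from the article, because it depends on correlation and on a selection rule that is not stated.

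The documents do not show that 700 is too small for the study, nor that false risk factors are certain. The incidence half of the aim is unaffected. The change should be made, but it is one of wording and analysis rather than design.

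**What to change.** - **Sample size estimation:** delete the statement about the number of candidate risk factors, or replace it with the number of parameters 700 supports: about 5 to 13 for expected shrinkage of 0.9, with the assumed Nagelkerke R² (0.10 to 0.25) stated. Eight parameters, for example, require an R² of about 0.15.
- **Statistical analysis plan, main model:** before outcome data are examined, pre-specify one main Cox model within that number. Take one measure per construct (for example one anterior chamber depth and one angle-opening measure), chosen on clinical grounds and not by univariable p-values.
- **Statistical analysis plan, other variables:** label them exploratory, with false-discovery-rate control or a penalised model.
- **Use of the results:** if they are to define high-risk PACS, report discrimination and calibration corrected for optimism by bootstrapping the whole modelling procedure.

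If a fuller plan already contains a limited candidate set, citing it and its size would meet most of this. The cost is some wording and computing time, with no extra patients or visits. The drawback is that fewer variables carry confirmatory status.

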## Discussion

The BAPS is a multicenter, randomized, observational trial designed to explore the 5-year incidence of PACS progressing to PAC or PACG and to determine the risk factors for disease progression. The study hypothesizes that a subset of PACS patients, despite having similar initial presentations, might be predisposed to a faster disease progression, while others may remain relatively stable over time. By thoroughly analyzing and understanding the variables contributing to this divergence in disease course, we aim to identify high-risk PACS individuals who are more likely to developing PAC or PACG. This could enable better clinical decisions regarding whether to opt for prophylactic treatment or continued observation for these high-risk patients.

Although awareness of glaucoma screening is gradually increasing, the prevalence of PAC and PACG is as high as 1% in China (5, 6). Since the mid-1970s, LPI has been considered the first-line therapy for PAC and PACG (29). However, several randomized trials of screening and prophylactic LPI in patients with PACS conducted in Asia have reported no benefit in preventing vision loss due to glaucoma or in slowing the progression of the disease (17, 30). An Indian study demonstrated that LPI accelerates the progression of cataracts over a 6-years follow-up (31). Additionally, LPI may cause structural zonular damage and occult lens subluxation (32). Despite eye care providers being aware of these potential complications, a large number of LPI are still performed due to the fear of PACS rapidly evolving into PAC or PACG (33, 34). Therefore, identifying patients with high-risk PACS is critical both for reducing complications from LPI and for mitigating damage to visual function from PAC and PACG.

Alsbirk et al. conducted a study on angle closure in the population of Greenland Eskimos, who exhibited a high incidence of PACG, similar to conditions observed in Southeast Asian populations (15). The study reported that at a 10-year follow-up, 16% (95% CI, 8.5–26.3%) of 75 eyes with PACS progressed to the equivalent of ISGEO PAC (synechial PAC) or PACG (acute or chronic). Slit-lamp screening (LACD and ACD) was effective in identifying a subgroup at risk for developing PACG over the 10-year follow-up (15). However, the study has two significant limitations. First, the use of slit lamp alone to assess LACD and ACD is subjective and unreliable. Second, the study did not use the ISGEO classification, as it was conducted earlier and applied previous diagnostic criteria (35). Consequently, it cannot provide valuable guidance for the treatment of PACD. Wishart and Batterbury’s study reported that 36% of patients in the narrow angle group developed PACG over an average 4-year follow-up period (36). This study faced similar issues as Alsbirk et al.’s study, and it was not observational, as it employed IOP-lowering medications for patients. Therefore, it could not provide valuable insights into the natural history of PACD.

An Indian prospective study demonstrated that 22% (95% CI, 9.8–34.2%) of patients with PACS developed PAC, but no PACG were observed during the 5-year follow-up. The study identified bilateral PACS as a clinical risk for disease progression, but no biometric characteristics were found to be significant (10). The sample size in this study was relatively small, with only 50 PACS were examined, and the participants were not consecutively enrolled. Instead, the patients previously diagnosed as PACS in other studies were invited for a review examination. Consequently, the incidence of disease progression may be biased. Additionally, the absence of PACS cases progressing to PACG over the 5-years period is inconsistent with clinical experience.

Several other population-based studies conducted in China (11, 12) and Singapore (13) share similar aims and designs with this study. They have numerous advantages, such as being multicenter, having large sample size, offering valuable clinical significance, employing scientific study design, and incorporating long follow-up periods. However, none of these studies included UBM in their baseline examinations. Anterior segment imaging techniques, including AS-OCT and UBM, has advantages over gonioscopy (37), such as providing more detailed parameters of the iris (26), lens (38), and anterior chamber (39). Increasing evidence suggests that structures behind iris, such as the ciliary body (26, 40) and VZ (41), play important roles in the pathogenesis of PACD. UBM is the only technique capable of providing sufficient details of these posterior structures. To the best of our knowledge, this study is the first to explore the natural course of PACD including UBM data.

## Conclusion

The BAPS is a large-scale, multicenter, clinic-based trial conducted in an urban setting. The study aims to provide valuable data on the 5-year incidence of PACS progressing to PAC or PACG and to determine the risk factors for disease progression. Additionally, this study may help redefine high-risk patients with PACS and offer guidance on assessing the benefits and risks of PACS treatment.

## Ethics statement

This study has been approved by the Ethics Committee of Peking University People’s Hospital and follows the tenets of the Declaration of Helsinki. The patients/participants provided their written informed consent to participate in this study.

## Glossary

BAPS: Beijing Angle Closure Progression Study
PACS: primary angle-closure suspect
PAC: primary angle-closure
PACG: primary angle-closure glaucoma
PACD: primary angle-closure diseases
IOP: intraocular pressure
PAS: peripheral anterior synechiae
LPI: laser peripheral iridotomy
UBM: ultrasound biomicroscopy
PVA: presenting visual acuity
BCVA: best corrected visual acuity
LogMAR: logarithm of the minimal angle of resolution
LOCS III: Lens Opacity Classification System III
LACD: limbal anterior chamber depth
AL: axial length
ACD: anterior chamber depth
LT: lens thickness
WTW: white-to-white
AS-OCT: anterior segment-optical coherence tomography
RNFL: retinal nerve fiber layer
VF: visual field
SS: scleral spur
VZ: vitreous zonule
PVZ INS-LE: posterior vitreous zonule insertion zone and posterior lens equator
ISGEO: International Society of Geographical and Epidemiological Ophthalmology
